### Objectives

The aim of the CAPEDP trial was to evaluate, in young primiparous mothers presenting vulnerability factors associated with greater likelihood of child mental health disorders, the impact on infant mental health of a home-visiting program conducted by trained psychologists and targeting the major modifiable determinants of infant mental health.

The program evaluated three primary outcomes: child mental health at the age of two, as well as two potential mediating variables: maternal postnatal depression at three months postpartum and the quality of the home environment when the child was 12 months old.

Secondary objectives included evaluating the impact of the intervention on: maternal postnatal depression at 6 months postpartum, infant attachment quality at 18 months of age, the mother’s quality of attachment at her child’s second birthday, her knowledge and use of social, medical and educational support services, her perception of receiving support from her own personal network, her parenting perceptions and behaviour, the child’s psychomotor development, sustained withdrawal behaviour of the child at 18 months, the mother’s knowledge concerning child development, her parental stress concerning caring for her child, her access to training and employment, her own psychological health and, in the intervention group, the working alliance between the mother and the home-visiting team (Table 1).

**Table 1 T1:** Outcome criteria and assessment schedule

**Instrument**	**Concept measured**	**Validation**	**Outcome assessor**	**Structure of instrument; scoring**	**Time of measurement**					
			**Place of evaluation**		**Prenatal**	**3 mths after birth**	**6 mths after birth**	**12 mths after birth**	**18 mths after birth**	**24 months after birth**
Edinburgh Post- partum Depression Scale (EPDS)	Pre and pospartum depression	Cox et al., 1987 [40]	Mother during home visits	10 items, 4 point-Likert scales (0–3)	X	X	X	X		
		French validation: Guedeney & Fermanian, 1995 [41]		Range 0–30						
				Higher scores indicate higher levels of depressive symptoms.						
Home Observation for the Measurement of the Environment (HOME) inventory	Quality of the home environment (quality and quantity of stimulation and support available to the child in the home environment)	Bradley & Caldwell, 1979 [42]	Assessment team during home visits	Designed for use during infancy (birth to age three).		X		X	X	

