### Study population

Eligibility criteria limited participation to mothers in situations of medium to high vulnerability with regard to their future child’s mental health. All consecutive women consulting in the second trimester of pregnancy (from 12 to 27 weeks of amenorrhea) in ten public maternity wards were assessed for eligibility. Pregnant women were eligible if they were: living in the intervention area (Paris and its inner suburbs); sufficiently fluent in French to give valid informed consent, benefit from the intervention and participate in assessment sessions; less than 26 years old; first time mothers; less than 27 weeks pregnant at their first home visit assessment session; eligible for legal national health insurance or its equivalent for non-French participants (as required by French law on clinical research). They also had to declare at least one of the three following criteria: 1) having less than twelve years of education, 2) intending to bring up their child without the presence of the child’s father, and 3) having low income, defined as being eligible for French social welfare health insurance (*Couverture Maladie Universelle Complémentaire*) i.e. with an income less than or equal to 850 euros a month or, for undocumented migrants, Government Medical Aid (*Aide médicale d’Etat*).

Exclusion criteria were: women who would be impossible to follow up, such as Roma, gypsies, travelers, the homeless, or temporary refugees; women already receiving sustained social or medical care for other reasons than the above inclusion criteria (such as addictions or mental or physical disorders requiring close long-term follow-up); and women who did not consent to participate.

Participation in the study was proposed to eligible women in the waiting rooms of each maternity hospital, prior to a prenatal appointment. During this interview or at a second appointment if she asked for more time to make up her mind, the future participant signed the informed consent form.

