### Randomisation and masking

After completing baseline screening and informed consent procedures, participants were randomly assigned in a 1:1 ratio to either the CAPEDP intervention or the usual care group using a computer-generated randomisation sequence, stratified by recruitment centre, with random block sizes of 2, 4 or 6 participants. This sequence was centrally generated by the Clinical Research Unit of Bichat Hospital, Paris, France. Assignment of participants was concealed using centralized randomisation through fax in the Clinical Reseach Unit. Investigators thus had no knowledge of the next assignment in the sequence in this open label trial. Investigators, psychologists performing the CAPEDP intervention and participants were blinded to assignment before, but not after, randomisation, as per the open-label design. However, in accordance with PROBE methodology, the outcome assessors were blinded to assignment and no investigators, psychologists or participants had any knowledge of aggregate outcomes at any point during the course of the study.

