### Statistical analysis

#### Determination of sample size

The trial was designed to establish whether the CAPEDP intervention was superior to usual care in terms of postnatal maternal depression prevention as assessed using the EPDS, the quality of the home environment assessed with the HOME, and child psychopathology, assessed using the CBCL 1½-5.

Regarding the prevention of postnatal maternal depression, assuming a mean of 12.1 on the EPDS (SD 4.6) for the usual care group [41], 113 participants per study group would be sufficient to detect a 2-point decrease in the EPDS with 90% power at a 2*-*sided significance level of α = 5%.

Regarding quality of the home environment, assuming a mean of 25.5 on the HOME (SD 4.3) for the usual care group [72], 99 participants in each study group would provide 90% power at a two-sided α = 5% to detect a 2-point increase in the HOME.

Regarding infant psychopathology, assuming a mean score of 48.5 on the CBCL 1½-5 (SD 8.95) for the usual care group [73], 189 participants in each study group would provide 90% power at a two-sided α = 5% to detect a 3-point difference in the CBCL 1½-5.

To account for possible patients lost to follow up and have sufficient power to answer all three primary objectives, the project planned to recruit 440 families.

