##### Primary analyses

The data will be analyzed according to the modified intention-to-treat principle: all participants are taken into account within their particular assignment group whatever might have happened during the study, and all randomized participants that have at least one assessment visit within the first year of follow-up will be included for analysis. Missing data will be handled using multiple imputation and sensitivity analyses will be conducted. The between-group absolute differences in the EPDS score when the child is 3 months old, the HOME score at 12 months and the CBCL score at 24 months will be analyzed using Student’s t tests.

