##### Secondary analyses

Data that are normally distributed will be analyzed using Student’s t test for continuous data, and chi-square test for categorical data, if the corresponding assumptions are fulfilled. If not, appropriate non-parametric methods will be used. In the intervention group, compliance to the CAPEDP program will be described by the proportion of planned home visits that actually took place performed reported to those scheduled. All statistical analyses will be considered significant at the 5% confidence limit using 2-sided tests. SAS software (version 9.1) will be used for statistical analyses.

More than 5,000 home visits were scheduled. A qualitative and quantitative analysis is being performed on the home visitors’ case notes to evaluate the extent to which the intended intervention program was effectively implemented or not. Case notes are analysed with regard to the frequency of themes that were declared as discussed during each home visit as well as the home visitors’ subjective perceptions of the visit.

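### The primary t tests leave out the stratification factor and known prognostic factors: valid, but they give up some precision

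*Protocol article*

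**What the plan says.** Under Primary analyses, the protocol article compares the arms on the EPDS at 3 months, "the HOME score at 12 months and the CBCL score at 24 months will be analyzed using Student’s t tests". No centre term or covariate is named. Participants are kept in the arm to which they were assigned, and missing data are to be multiply imputed.

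Under Randomisation and masking, "participants were randomly assigned in a 1:1 ratio", with the sequence "stratified by recruitment centre, with random block sizes of 2, 4 or 6 participants". Recruitment was from second-trimester consultations: women "in ten public maternity wards were assessed for eligibility" (Study population).

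That section also makes age under 26 an eligibility condition. It requires at least one of three factors: short education, raising the child without the father, or low income. All four items are therefore known before allocation. The Background presents young first-time motherhood, parents living apart, low socioeconomic status and low education as linked to child disorder.

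Table 1 (Objectives) lists the EPDS as a measure of "Pre and pospartum depression" and marks a prenatal assessment. HOME and CBCL have no prenatal measurement. The Discussion states that randomisation came before the first assessment visit and that an appreciable number of women withdrew before any data were collected.

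**The concern.** Stratifying by centre balances the arms on centre, so differences between centres contribute little to the true sampling error of the treatment contrast. A two-sample t test still counts those differences as noise, and its standard error is too large to the extent that centres differ. Leaving out prognostic covariates has a related cost: variance that they could explain stays in the residual.

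What is at stake is the width of three confidence intervals and, for the CBCL, some power. The CBCL is the outcome that sets the sample size and the last to be measured, and the Discussion already reports attrition as a problem. The method is stated outright, so this is a choice the document makes and not a detail left to an analysis plan.

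**Working it through.** **Inputs from the documents.** Alpha: "All statistical analyses will be considered significant at the 5% confidence limit using 2-sided tests" (Secondary analyses). From Determination of sample size: EPDS SD 4.6, difference 2; HOME SD 4.3, difference 2; CBCL SD 8.95, difference 3; 90% power; 113, 99 and 189 per arm; 440 families in total. Ten centres, 1:1 allocation.

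**Assumed, because the documents give no figure.** Share of variance between centres: 5 to 10%. Multiple correlation R of the screening factors with outcome: 0.1 to 0.3. Correlation r of prenatal with 3-month EPDS: 0.3 to 0.6.

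**1. The plan's own figures.** For the EPDS the article states "assuming a mean of 12.1 on the EPDS (SD 4.6) for the usual care group" and that "113 participants per study group would be sufficient to detect a 2-point decrease in the EPDS with 90% power". The two-sample noncentral t calculation gives:

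- EPDS: 2/4.6 = 0.435, n = 112.1, rounded up to 113
- HOME: 2/4.3 = 0.465, n = 98.1, rounded up to 99
- CBCL: 3/8.95 = 0.335, n = 188.003, rounded up to 189

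All three reproduce. The sample size is right for the unadjusted test.

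**2. Which n to use.** One sample serves all three outcomes, and the CBCL sets it at 189 per arm (378 in total). Recruiting 440 allows a loss of 62/440 = 14%. Gains are therefore evaluated at 189 per arm.

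**3. Centre.** If centres carry a share s of the variance, the unadjusted SE is too large by a factor 1/√(1 − s), and the true alpha is 2[1 − Φ(1.96/√(1 − s))].

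- s = 0.05: factor 1.026, alpha 4.4%
- s = 0.10: factor 1.054, alpha 3.9%

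A simulation (10 centres of 38, permuted blocks of 2, 4 or 6 within centre, 8,000 runs per setting) gave a type I error for the t test of 4.6% and 4.2% at these shares. At the CBCL effect, with shares from 1 to 10%, adding centre raised power by 0.2 to 1.6 percentage points.

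**4. Screening factors, CBCL at 189 per arm.** Residual SD = 8.95·√(1 − R²).

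| R | Residual SD | Power |
|---|---|---|
| 0 | 8.95 | 90.2% |
| 0.1 | 8.905 | 90.4% |
| 0.2 | 8.769 | 91.3% |
| 0.3 | 8.538 | 92.6% |

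HOME power at 189 per arm is already 99.5% unadjusted.

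**5. Prenatal EPDS, 3-month EPDS at 189 per arm.** Unadjusted power is 98.8%. The half-width of the 95% interval is 1.966 × 4.6 × √(1 − r²) × √(2/189).

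| r | Half-width (points) |
|---|---|
| 0 | 0.93 |
| 0.3 | 0.89 |
| 0.5 | 0.81 |
| 0.6 | 0.74 |

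**The case against.** The strongest reply is that nothing here is wrong: the t test controls type I error, the design calculation matches it, and the gains rest wholly on assumed correlations and centre shares. That stands, and it limits the weight of the point. It does not remove it, because the stratification factor and screening items are already in hand and adjusting for them needs no new data.

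A second reply is that eligibility restricts the screening factors: every woman is under 26, a first-time mother and has at least one of the three vulnerability criteria. Their R may well be low. That also stands, and is why the assumed range stops at 0.3.

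A third is that covariates can enter the imputation model whatever the final test. That is true, so a more plausible missing-at-random assumption is not by itself a reason to change the test. The precision argument is separate and remains.

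Three stronger readings are tempting but unsupported.

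- A reader might infer that the trial is not analysed as randomised. Primary analyses keeps women in their assigned arm; only the stratification factor is omitted.
- A reader might infer that every woman has a prenatal EPDS. Table 1 only schedules it, the Discussion reports early withdrawals, and one assessment visit in the first year is enough to enter the analysis.
- A reader might evaluate the EPDS gain at 113 per arm, where power would rise from 90% to between 93% and 98%. The trial is sized for 189 per arm; a fall to 113 of 220 would mean a loss of 107/220 = 49% by 3 months.

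**Conclusion.** The point holds as a moderate matter of efficiency. The t tests are valid and slightly conservative, but they ignore the factor on which allocation was stratified and prognostic information known before it. On the assumed ranges, the omission of centre makes the SE about 3 to 5% too large, with a true alpha of about 4 to 4.5% by formula and simulation together. The screening factors add between 0.2 and 2.4 percentage points of CBCL power. For the EPDS the benefit is a narrower interval and hardly any power. The document supplies none of these correlations or shares, so only the direction of the effect is firm. No stated sample size needs correction.

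**What to change.** Replace the three t tests with a linear model fitted within the planned multiple imputation, containing arm, recruitment centre and the four items known at screening: education, father's absence, low income and maternal age. Report the adjusted mean difference as the primary result and keep the unadjusted t test as a sensitivity analysis.

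For the 3-month EPDS, add the prenatal EPDS from the scheduled week-27 assessment. Define the permitted window by calendar or gestational time, identically in both arms, and impute missing values. A rule that accepts only values taken before the first programme visit should be avoided: controls have no such visit, so it could discard values in the intervention arm only. Because this score is collected after randomisation in an open-label trial and some women will lack it, also show the EPDS model without it.

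The cost is a change of wording in the analysis section and some extra programming. No new data, visits or participants are needed. The change should be fixed before outcomes are compared by arm.

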##### Secondary analyses

Data that are normally distributed will be analyzed using Student’s t test for continuous data, and chi-square test for categorical data, if the corresponding assumptions are fulfilled. If not, appropriate non-parametric methods will be used. In the intervention group, compliance to the CAPEDP program will be described by the proportion of planned home visits that actually took place performed reported to those scheduled. All statistical analyses will be considered significant at the 5% confidence limit using 2-sided tests. SAS software (version 9.1) will be used for statistical analyses.

More than 5,000 home visits were scheduled. A qualitative and quantitative analysis is being performed on the home visitors’ case notes to evaluate the extent to which the intended intervention program was effectively implemented or not. Case notes are analysed with regard to the frequency of themes that were declared as discussed during each home visit as well as the home visitors’ subjective perceptions of the visit.

### Ethical principles and safety

The study was designed and carried out in accordance with the principles of the Declaration of Helsinki, 5^th^ revision [74]. The study protocol was approved for all centres by the Institutional Review Board ‘Comité de Protection des Personnes Ile de France IV’ (IRB authorisation 2006/37). Written informed consent was obtained from all participants before inclusion. The trial is registered as ClinicalTrials.gov number *NCT00392847.*

## Discussion

The CAPEDP study is the first large-scale attempt in France to assess the impact of a home-visiting program on infant mental health in a highly vulnerable urban sample, thus replicating to a certain extent Old’s Elmira study in the US, but with a more systematic focus on the major modifiable determinants of infant mental health, particularly with regard to attachment security, the development of healthy mother-child relationships, pre and postnatal maternal depression, parenting skills and the quality of the home environment, and knowledge of community health and social care resources. A major specificity of the program is that the French context is characterized by easy access for all to community-based perinatal medical services, mental health services and social support, even for illegal immigrants. Hence, a significant aspect of the intervention was to encourage and help mothers to use the existing care system.

The second major specificity of the CAPEDP intervention was that, unlike other prevention programs based on home-visiting by nurses or trained community members, the entire home-visiting intervention was conducted by qualified psychologists, with the hypothesis that professionals who are more highly trained in psychology will be more skilled in identifying and acting upon the different potential determinants of infant mental health in multi-risk situations.

A limitation of the present study is that the control group cannot be considered to have received no intervention, on the one hand because “care as usual” is particularly generous in the French health and social care system and, on the other, due to the fact that the evaluation process could well be considered to be an intervention in itself, creating a Hawthorne effect. Furthermore, attrition is well-known to be a major challenge for home-visiting programs in vulnerable families [75-77]. In spite of considerable efforts to optimise adherence, CAPEDP is proving to be no exception to the rule. This is all the more so in that, in the French context, access to such a generous care system may also have an unfavourable impact on adherence, with mothers considering that they have all the help they need or preferring local community support to potentially stigmatising home visits by psychologists.

Another limitation is that randomisation was performed at inclusion, rather than after the first assessment visit. A significant number of randomized women withdrew their consent to participate before any data had been collected. This will necessarily result in a modified intent to treat analysis, a classical intent to treat analysis being impossible.

Furthermore, it must be underlined that women who were not fluent enough in French to give informed consent to participate or who were already receiving other types of clinical interventions were not eligible for inclusion in the present study. Similarly families for whom home-visiting would be impossible, for example Roma, gypsy or traveller families, transient refugees or homeless women were excluded. Generalising from results from this study to all mother-child dyads in multi-risk social situations will therefore be hazardous.

